### Outcomes

The primary outcome is biochemically validated abstinence at 6 months after treatment initiation using exhaled carbon monoxide (< 4 ppm) and salivary cotinine (< 10 ng/ml) [41]. Secondary outcomes include (1) biochemically validated abstinence at 3 months (end of treatment), (2) self-reported past 7 days abstinence, (3) smoking reduction by at least 50% of baseline consumption, (4) quit attempt (abstinence for ≥24 h), and (5) smoking cessation services use, defined by any use of provided treatments (e.g. counselling, medication, acupuncture).

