### Interventions

All participants receive face-to-face brief interventions at baseline followed by 3 months of mHealth support via an instant messaging app. In phase 1 (i.e. the first month after enrolment), the PIM group receives personalised chat-based behavioural support and the RIM group receives generic, fix-scheduled messages on smoking cessation. We modify the subsequent treatments depending on the smoking status at 1-month follow-up and the second group allocation (Fig. 1 and Table 1).

**Table 1 Tab1:** Adaptive intervention strategies embedded

	Adaptive intervention strategy			Type of strategy	Subgroup
	Phase 1 intervention	Tailoring variable assessed at 1 month (7-day PPA)	Phase 2 intervention		
1	PIM	Smoking	PIM+OCI	Adapt	A
2	PIM	Smoking	PIM	Maintain	B
3	PIM	Quitting	PIM	Maintain	C
4	RIM	Smoking	PIM	Adapt	D
5	RIM	Smoking	RIM	Maintain	E
6	RIM	Quitting	RIM	Maintain	F

Abbreviations: *PIM*, personalised instant messaging; *OCI*, optional combined intervention; *RIM*, regular instant messaging. Phase 1 intervention will be conducted during the first month after enrolment and phase 2 intervention will be conducted during the second and third months after enrolment

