PIM intervention is delivered by smoking cessation counsellors well-trained in using transtheoretical behaviour change model (TTM) [29] and motivational interviewing (MI) [30]. The frequency and content of messages are guided by the TTM model and behavioural change techniques (BCTs) are used to maximise self-regulation and promote adjuvant activities for quitting [31]. MI counselling skills are used to increase their personal motivation in quitting. PIM intervention aims to engage and motivate participants to develop a personalised quit plan and facilitate further combined behavioural and pharmacological treatments for abstinence.

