#### Optional combined interventions (OCI)

For non-responders in the PIM group randomised to receive OCI, smoking cessation counsellors explain and assist them to opt for sequent interventions at 1-month follow-up. Available intervention options include (1) multi-media messages, (2) nicotine replacement therapy sampling, (3) financial incentive for active referral, (4) phone counselling, and (5) family/peer support group chat. OCI participants who lost to follow-up or cannot make the decision at 1 month receive multi-media messages (default option) in addition to the PIM. Those who decline OCI intervention, if any, maintain the initial treatment.

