##### Nicotine replacement therapy sampling (NRT-S)

Previous RCTs found that NRT-S effectively increased quit attempts and abstinence [32, 33]. OCI participants who are willing to use medication assistance receive 1-week dosage of NRT-S (gum or patch) and used a card (Additional file 1: Appendix 1) containing instructions and potential side effects. Cessation counsellors confirm with participants for mailing address and contraindications to NRT use, including (1) recent (within 2 weeks) heart attack or severe arrhythmia, (2) unstable angina, or (3) pregnancy [34]. The dose of the NRT-S depends on participants’ daily cigarette consumption: 2 mg nicotine gum or 14 mg nicotine patch for those who smoke < 20 cigarettes per day and 21 mg nicotine patch for those who smoke ≥ 20 cigarettes per day. NRT use and potential side effects will be briefly explained based on a standardised script of the product instruction [35]. Cessation counsellors and research staff monitor side effects of NRT-S use through instant messaging interaction and telephone follow-ups. All adverse events will be reported to the IRB. Participants interested in a full course of NRT treatment will be referred to smoking cessation services.

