**Table 3 Tab3:**
[figure not shown]
The schedule of enrolment, interventions, and assessments

^a^Sociodemographic characteristics include age, sex, education level, number of children, occupation, marital status, and household income

All participants are followed-up at 1, 2, 3, and 6 months to monitor the smoking and quitting behaviour, smoking cessation service use, and intervention engagement. Participants are considered lost to follow up after 7 missing calls and 1 voice message at different time and day of the week. Self-reported 7-day PPA at 3- and 6-month follow-up are invited for biochemical validation. Financial incentive of HK$500 (≈ US$64) will be given to both groups for passing the validation at 3 and 6 months (total HKD1000≈US$128) to increase the participation rate [20].

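### The cotinine criterion counts abstinent participants still using NRT at validation as smokers, and the plan has no rule or sensitivity analysis for them

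*Protocol article*

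**What the plan says.** The Outcomes section states: "The primary outcome is biochemically validated abstinence at 6 months after treatment initiation using exhaled carbon monoxide", with a cut-off of 4 ppm, and salivary cotinine, with a cut-off of 10 ng/ml. The 3-month validated outcome is listed there as secondary, although the Abstract calls both time points primary. Under data collection, "Self-reported 7-day PPA at 3- and 6-month follow-up are invited for biochemical validation". Neither place says how a participant who is using NRT on the test day is classified.

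On NRT, the plan says that "OCI participants who are willing to use medication assistance receive 1-week dosage of NRT-S (gum or patch"), and that "Participants interested in a full course of NRT treatment will be referred to smoking cessation services". Both sentences stand in the NRT sampling section, under OCI, which only Subgroup A receives. Another OCI option is a prepaid HK$100 for a verbal commitment to use a cessation service within 2 months. PIM itself is meant to "facilitate further combined behavioural and pharmacological treatments for abstinence".

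Two further statements pull the other way. The Baseline interventions section refers every participant in both arms to a cessation service, with boosting at 1 and 2 months for those who fail to quit or relapse. The Outcomes section gives medication as an example of what such services provide.

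**The concern.** Cotinine is formed from nicotine whatever its source. A person who no longer smokes but uses a patch or gum can pass the CO test, fail the cotinine test and enter the analysis as a smoker. This is a stated rule giving the wrong answer for identifiable people, in a trial that offers and encourages NRT. It is not a detail left out for brevity.

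If current NRT use at the test were equal between the groups compared, the rule would cost power but leave the risk ratio unchanged. If use were higher in A, or across A+B+C, the rule would pull the estimated effect towards no difference in both the main and the co-primary comparison, because it would count use of an encouraged treatment as failure.

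**Working it through.** **1. Can the trial-supplied sample cause the failure?** Table 2 marks NRT sampling once, read as week 5, consistent with the statement that "phase 2 intervention will be conducted during the second and third months after enrolment". The gap to the tests is 12 − 5 = 7 weeks for month 3 and 26 − 5 = 21 weeks for month 6. Assume a starting cotinine of 300 ng/ml and a half-life of 16 to 40 hours (neither is in the document). With the slowest half-life, the level after 7 weeks is 300 × 0.5^(7×7×24/40), about 4 × 10⁻⁷ ng/ml, against a cut-off of 10. A sample used when supplied therefore has no effect at either test. Only NRT still in use at the test matters, and that would come mainly from outside services.

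**2. Reproduce the plan's figure.** Inputs from the sample size section: control rate 5.0%, risk ratio 1.83, so 0.05 × 1.83 = 9.15%; 600 per arm; 5% error rate, taken as two-sided. With the pooled-variance z-test,

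n = [1.96·√(2p̄q̄) + 0.842·√(p₀q₀ + p₁q₁)]² / (p₁ − p₀)², with p̄ = 0.07075,

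= (0.711 + 0.304)² / 0.0415² ≈ 599 per arm. Power at 600 per arm is 0.80. The stated size reproduces and does not depend on the NRT point.

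**3. Illustrate unequal use.** Let f be the excess share of Subgroup A quitters on NRT at the test. It is an assumption, because the document gives no such rate. Take 9.15% as the quit rate throughout the PIM arm and A as 402 of its 600 participants. Then:

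- observed rate in A+B+C = 9.15% × (1 − f × 402/600)
- observed rate in A = 9.15% × (1 − f)
- expected quitters in A = 402 × 0.0915 = 36.8

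| f | A quitters misread (36.8 × f) | Rate in A+B+C | Main risk ratio | Main power | A vs E risk ratio |
|---|---|---|---|---|---|
| 0 | 0 | 9.15% | 1.83 | 0.80 | 1.83 |
| 2% | 0.7 | 9.03% | 1.81 | 0.78 | 1.79 |
| 5% | 1.8 | 8.84% | 1.77 | 0.75 | 1.74 |
| 10% | 3.7 | 8.54% | 1.71 | 0.68 | 1.65 |

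No power is given for A versus E. The plan does not state the rates behind its 0.81, and the main-comparison rates do not reproduce it: at 402 and 416 they give 0.64. That is a separate sample-size matter.

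**4. Illustrate equal use.** If 10% of quitters in each arm are on NRT at the test, the rates become 8.235% and 4.5%. The ratio stays 1.83 and power falls to 0.76.

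**The case against.** A reader might infer that, because NRT is supplied only in OCI, the primary outcome is biased against the intervention. The document does not support that step.

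- The supply is a single optional week, ended long before either test. It is one of five options and not the default: "OCI participants who lost to follow-up or cannot make the decision at 1 month receive multi-media messages (default option) in addition to the PIM".
- Longer NRT comes from services to which both arms are referred. RIM messages cover the same content as PIM's regular messages, including information about services.
- PIM's encouragement of drug treatment also reaches Subgroup D, which sits in the comparator of the main comparison.

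The size is equally open. The plan defines both the 5.0% and the 1.83 as validated abstinence, so some loss of NRT users may already be inside them. Self-reported 7-day abstinence, which cotinine cannot affect, is a secondary outcome and offers a partial check. The full protocol may also contain a rule that the article omits.

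Making CO alone the primary criterion for reported NRT users would carry its own risk. It relaxes the test mainly where NRT is offered, and passing validation pays HK$500 each time.

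Most of this stands. It removes the claim of demonstrated bias and the case for changing the primary definition. It does not remove the misclassification of current NRT users, or the OCI-only incentive and full-course referral that could make their number unequal.

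**Conclusion.** The rule as written misclassifies abstinent participants who are using NRT at validation. A differential effect against A and A+B+C is plausible but not shown. It is more plausible at 3 months, because a course begun through an OCI referral after month 1 could still be running then.

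For an excess of 2% to 10% among Subgroup A quitters, the main risk ratio would fall from 1.83 to between 1.81 and 1.71, and power from 0.80 to between 0.78 and 0.68. In expected numbers that is about one to four people. These figures rest on the assumed excess, on a uniform 9.15% quit rate in the PIM arm, and on treating the planned validated rates as if no NRT user had yet been lost. With equal use the ratio does not move. The point deserves a check built into the analysis, not a new primary outcome.

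**What to change.** - Record NRT use in the week before each validation, at 3 and 6 months.
- Keep CO below 4 ppm plus cotinine below 10 ng/ml as the primary definition for everyone.
- Prespecify a sensitivity analysis of both primary comparisons, and of the 3-month outcome, in which reported current NRT users are classified by CO below 4 ppm alone.
- Report by subgroup (A to F) how many participants this reclassifies.

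The cost is one question and one further analysis. CO alone may miss light smoking or misreported NRT use, which is why this should be a sensitivity analysis and not the primary result.

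Timing limits the options. The qualitative interviews are planned for after the 6-month follow-up, and the Trial status section says they are in progress, so outcome collection may be finished. If NRT use was not recorded, use the cessation-service use collected at follow-up as a rough substitute and label the analysis post hoc.

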#### Primary comparison

The main primary comparison is to between participants receiving PIM with additional OCI (Subgroup A+B+C) and participants receiving RIM with additional PIM (Subgroup D+E+F) (see Fig. 1). The co-primary comparison is PIM enhanced by OCI (Subgroup A) compare to RIM alone (Subgroup E) among non-responders to the phase 1 intervention. The hypothesis is that participants non-responding to the phase 1 mHealth interventions will benefit from additional personalised support.

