The adaptive approach is a scientific concept of stepped treatment intended to address patients’ unmet needs [13], which resembles the clinical practice of chronic disorder management such as depression, weight loss, and smoking cessation [14]. An assumption of adaptive interventions is that greater support (i.e. more intensive intervention) may lead to superior study outcomes and would be prescribed for all if resources are allowed [14]. Trials in reported use of adaptive design are increasing but mostly on drug development and dose-finding study [15]. Adaptive studies on smoking cessation are scant and no evidence-based guidelines for the clinical management of tobacco dependence treatment. The Sequential, Multiple Assignment, Randomised Trial (SMART) is an experimental design developed explicitly to optimise adaptive interventions and thus could be used to facilitate the development of more personalised mHealth cessation support [13].

In this study, the SMART design is proposed to optimise mHealth intervention in community-recruited smokers in terms of (1) altering the intensity of intervention to improve abstinence, (2) test the effectiveness of different adaptive mHealth strategies combined with evidence-based tobacco treatments, and (3) utilise self-determination to explore a more personalised smoking cessation treatment algorithm. Evidence showed that providing more choices of cessation services (e.g. nicotine replacement therapy, text messaging) increased quit attempts and long-term abstinence [16]. In this study, we provide optional combined cessation interventions based on smokers’ smoking status and preference. These interventions, including multimedia message [17, 18], nicotine replacement therapy sampling [19], active referral plus financial incentive [20], phone counselling [21], and social support [22], are evidence-based and supported by our previous trials. This study protocol describes the design and rationales of an adaptive trial that aims to evaluate the effectiveness of personalised mHealth intervention on quitting among community-recruited smokers.

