### Randomisations and blinding

Within 3 days after baseline recruitment, participants are computer-randomised by an investigator who is not involved in recruitment. The first randomisation assigns participants into the PIM or RIM group with a random permuted block size of 2, 4, and 6 in 1:1 allocation ratio. At 1 month, a second randomisation is conducted among non-responders (smoke for even a puff in the past 7 days). In the PIM group, non-responders are further randomised to receive OCI or continue PIM with a block size of 4, 8, or 12 to ensure an allocation ratio of 3:1. Non-responders in the RIM group are randomised to receive PIM or continue RIM, with an allocation ratio of 1:3. The different allocation ratio in the second randomisation is designed to maximise the statistical power to compare OCI versus RIM, which is the co-primary comparison of the current trial (refer to 2.7). Smoking cessation counsellors, outcomes assessors, and statistical analysts are blinded to the group allocation.

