### Sample size and power calculation

G*Power is used to calculate the sample size [39]. The required sample size is based on the primary comparison of validated quit rate at 6 months (Fig. 1, Subgroup A+B+C versus Subgroup D+E+F). A meta-analysis showed the risk ratio of mHealth intervention on smoking cessation for biochemically validated abstinence at 6 months was 1.83 [40]. Assuming a 6-month biochemically validated quit rate of 5.0% in the in the D+E+F subgroups, 1200 participants will be needed (600 in each group) to achieve 80% power with a 5% false-positive error rate with an allocation ratio of 1:1.

In our previous mHealth trial, self-reported 7-day PPA at 1 month of the intervention and control group was 10.7% and 7.7%, respectively [6]. We estimate there will be 64 (= 600×10.7%) and 46 (= 600×7.7%) quitters for PIM and RIM groups at 1-month follow-up. Non-responders in the PIM (536, =600−64) and RIM groups (554, =600−46) will be reallocated by the second randomisation. Using an allocation ratio of 3:1 with a 5% false-positive error rate, a sample size of 402 (=536×3/4) in subgroup A and 416 (=554×3/4) in subgroup E has a power of 0.81 to test the co-primary outcome of validated quit rate at 6 months (Subgroup A versus Subgroup E).

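### The co-primary comparison of Subgroup A with Subgroup E is not randomised, and the embedded strategy of PIM followed by OCI for continuing smokers (A+C) is compared nowhere

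*Protocol article*

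**What the plan says.** Under Randomisations and blinding there are two steps. First: "The first randomisation assigns participants into the PIM or RIM group with a random permuted block size of 2, 4, and 6 in 1:1" allocation. Second, separately inside each arm and only among that arm's 1-month non-responders: "In the PIM group, non-responders are further randomised to receive OCI or continue PIM with a block size of 4, 8, or 12" (ratio 3:1), and "Non-responders in the RIM group are randomised to receive PIM or continue RIM, with an allocation ratio of 1:3". The unequal ratios are "designed to maximise the statistical power to compare OCI versus RIM, which is the co-primary comparison of the current trial".

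Under Primary comparison, the main contrast is between "participants receiving PIM with additional OCI (Subgroup A+B+C) and participants receiving RIM with additional PIM (Subgroup D+E+F"). The co-primary contrast follows: "The co-primary comparison is PIM enhanced by OCI (Subgroup A) compare to RIM alone (Subgroup E) among non-responders to the phase 1 intervention".

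The section defining response counts participants lost at 1 month as non-responders. The sample size section takes from an earlier trial that "self-reported 7-day PPA at 1 month of the intervention and control group was 10.7% and 7.7%, respectively".

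The secondary comparisons are A vs B, D vs E, and B+C vs E+F. One of the three purposes given for the design in the Introduction is to "test the effectiveness of different adaptive mHealth strategies combined with evidence-based tobacco treatments".

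**The concern.** Non-response at 1 month is an outcome of the phase-1 treatment. A is a random sample of those who did not respond to PIM, and E is a random sample of those who did not respond to RIM. No randomisation divides one common set of smokers between A and E. A smoker whom PIM would have helped in month 1 leaves the pool that feeds A, while the same kind of smoker stays in the pool that feeds E. The two groups have also had different treatment since baseline, so a difference at 6 months could come from selection, from PIM, from OCI or from any mixture of these.

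A co-primary efficacy claim would then rest on a contrast that cannot be read causally in non-responders. In addition, the adaptive strategy of most interest, PIM with OCI added for continuing smokers (A+C), is not set against RIM throughout (E+F) in any primary or secondary comparison.

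**Working it through.** **1. The plan's own figures.** The main comparison uses 5.0% in D+E+F and a risk ratio of 1.83, so 5.0% × 1.83 = 9.15% in A+B+C. A two-sided 5% test with 80% power (pooled normal approximation) needs 599 per arm, or 1198, which agrees with the stated 1200. The subgroup sizes also agree: 600 − 64 = 536 and 536 × 3/4 = 402 for A; 600 − 46 = 554 and 554 × 3/4 = 415.5, rounded to 416, for E. The stated power of 0.81 for A vs E comes without rates for A or E. Carrying over 5.0% and 9.15% gives 0.64, and 0.81 would need a risk ratio of about 2.05 if E is at 5%. The figure is therefore not reproducible from what is printed, but it is not shown to be wrong. Nothing below depends on it.

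**2. Who receives what in the main comparison.** OCI is allocated to 402/600 = 67% of the PIM arm. PIM is allocated to (554 − 416)/600 = 138/600 = 23% of the RIM arm. The contrast is initial PIM vs initial RIM, averaged over second-stage allocation in proportions set by the 3:1 and 1:3 ratios.

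**3. Selection in A vs E.** Assume that PIM never prevents a response. Then 10.7% − 7.7% = 3.0% of participants respond only to PIM: 600 × 0.03 = 18 of the 554 RIM non-responders, so f = 18/554 = 0.0325. Let m be their 6-month quit rate relative to the other non-responders, with no treatment effect at 6 months. The A/E risk ratio is then 1/(1 − f + f·m):

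| m | null A/E risk ratio |
|---|---|
| 2 | 0.97 |
| 3 | 0.94 |
| 5.5 | 0.87 |

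The value 5.5 comes from the earlier trial described in the Discussion: 69.8% of responders abstinent, against 100% − 87.3% = 12.7% of non-responders, and 69.8/12.7 = 5.5. A harsher assumption, 69.8% in PIM-only responders against 5% in the rest, gives E a rate of (0.893 × 5% + 0.03 × 69.8%)/0.923 = 7.1% and a null ratio of 5/7.1 = 0.70.

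**4. The opposite direction.** Suppose that OCI adds nothing, E quits at 5%, and PIM itself multiplies quitting among non-responders. With 402 vs 416 and a two-sided 5% test:

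| PIM risk ratio | probability that A vs E is significant |
|---|---|
| 1.2 | 0.09 |
| 1.4 | 0.23 |
| 1.6 | 0.41 |
| 1.83 | 0.64 |

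**5. The strategy contrast A+C vs E+F.** A participant in A or E had probability 1/2 × 3/4 = 3/8 of following that path (weight 8/3); one in C or F had 1/2 (weight 2). Dividing by 2 gives 4/3 and 1. Weights are needed because responders would otherwise be over-represented: 64/466 = 13.7% of A+C instead of 10.7%.

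For each strategy, with n_R responders, n_N non-responders and quit rates p_R and p_N, m = (n_R p_R + n_N p_N)/600 is now the strategy's mean quit rate. Its variance is V = [n_R(p_R(1 − 2m) + m²) + 0.75 n_N (4/3)²(p_N(1 − 2m) + m²)]/600².

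Example, with strategy rates of 5.0% and 9.15% and responder rates of 20% (RIM) and 30% (PIM). The non-responder rates are (30 − 46 × 0.20)/554 = 3.75% and (54.9 − 64 × 0.30)/536 = 6.66%. The variances are 0.0000978 and 0.0001697, so the standard error is √0.0002675 = 0.01636. Power is Φ(0.0415/0.01636 − 1.96) = 0.72. Responder rates of 10–30% (RIM) and 20–40% (PIM) give 0.70 to 0.73.

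For A vs E at the same overall rates, power is 0.64 if responders and non-responders quit alike. It is 0.37 if responders quit 5.5 times as often: E = 5%/(0.923 + 0.077 × 5.5) = 3.71% and A = 9.15%/(0.893 + 0.107 × 5.5) = 6.18%.

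**The case against.** A reader might infer that the trial has no valid primary analysis. The documents do not support that. A+B+C vs D+E+F compares whole phase-1 arms, is fully randomised, is what the 1200 were sized on, and answers the headline aim of evaluating personalised mHealth support. Its label is loose, but the subgroup letters make clear what is compared.

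A reader might also infer that selection would create a false claim of benefit. Under the assumptions in step 3 it runs against the intervention. With E at 5%, the chance of a falsely significant result favouring A is about 2.0% (m = 2) to 0.8% (m = 5.5), against a nominal 2.5%. Selection of this kind costs power. The route to a misread positive result is step 4.

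The protocol describes A vs E as PIM enhanced by OCI against RIM alone, restricts it deliberately to non-responders, tests OCI separately in A vs B, and plans models with and without adjustment for three baseline predictors. All this is fair, but adjustment for previous attempts, intention and dependence does not restore randomisation. Nor does reading A vs E as a package comparison, because each package's month-1 successes (C and F) are left out.

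The magnitude is assumption-based. The 5.5 ratio comes from an earlier trial and is applied here to validated outcomes in both arms. Losses counted as non-response could change the selection. The rates of 5.0% and 9.15% are whole-arm assumptions borrowed for strategies. The replacement has less than 80% power, and the second-stage ratios are already set. These points limit the numbers and the timing of the remedy; they do not make A vs E randomised.

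**Conclusion.** The concern holds in this form. A vs E is a comparison of two differently selected groups of non-responders and should not carry a co-primary efficacy claim. The expected 3-point response difference suggests a modest selection bias: a null risk ratio of about 0.97 to 0.87 if PIM never prevents a response and PIM-only responders quit at 2 to 5.5 times the others' rate, and 0.70 under the harshest rates tried. It runs against the intervention. Confounding of OCI with PIM runs the other way, so the net direction is unknown.

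The main comparison stands as a randomised test of initial PIM vs initial RIM, with an inaccurate label. The gap is that A+C vs E+F is absent from every listed comparison, although testing adaptive strategies is a stated purpose of the design.

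**What to change.** 1. Add A+C vs E+F, using all participants who follow each strategy, weighted 4/3 for A and E and 1 for C and F (equivalently 8/3 and 2), with robust standard errors. Make it the co-primary comparison if the change can be dated before outcomes are known. The Trial status section says that post-trial interviews, planned for after the 6-month follow-up, are in progress. If outcomes are already known, report it as an added analysis labelled post hoc.
2. Report A vs E as a secondary, non-randomised comparison, and do not interpret it as the effect of OCI.
3. Use A vs B as the randomised test of OCI in PIM non-responders.
4. Relabel A+B+C vs D+E+F as initial PIM vs initial RIM, averaged over second-stage allocation.
5. Revise the power statement. With 9.15% vs 5.0% assumed as strategy-level rates, weighted A+C vs E+F has power of about 0.70 to 0.73, and the shortfall from 80% must be stated.

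The cost is a dated change to the protocol or analysis plan and lower stated power. No new data or participants are needed.
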